### Data Handling

We have prepared a custom electronic case report form for the purposes of randomizing the practices to immediate or delayed access to STBD training at the point of opting in. The remaining data for use in this evaluation will be from routine health records (ie, weight management and diabetes care). Access to these data will be via the NHS Greater Glasgow and Clyde Safe Haven (already approved by the Local Privacy Advisory Committee). The data will be fully anonymized and accessed via a virtual private network. Access will be only for the duration of the analysis of the data for the evaluation.

### Review of the E-Learning, Patient Materials, and Evaluation

The STBD training and patient materials packages were developed over 2 years. The contents of the materials were developed by the NHS clinical team including a consultant physician, a GP, a consultant psychologist, specialist dietitian, and a health improvement specialist. Review has been extensive with patient materials reviewed by 7 patient volunteers (with type 2 diabetes and co-existing obesity), the training materials were reviewed by 3 specialist dietitians and 3 health improvement specialists, and then by 8 GPs who are based outside of NHS Greater Glasgow and Clyde. All materials were extensively reviewed by medical and marketing staff from AstraZeneca and Merck Sharp & Dohme to ensure they complied with the Association of British Pharmaceutical Industry code of practice. Evaluation plans had oversight from the evaluation team within NHS Greater Glasgow and Clyde Public Health. After the pilot study was conducted, the e-learning was independently reviewed and approved for continuous professional development points from both the Royal College of Nursing and the Royal College of General Practitioners.

### Approvals

Favorable ethical opinion was received from London – Bromley Research Ethics Committee. Sponsorship and management approval were received from NHS Greater Glasgow and Clyde. NHS Greater Glasgow and Clyde and Glasgow University Insurance and Indemnity will apply.

## Results

The first invitations for this evaluation were emailed in October 2017. Recruitment for this trial closed in April 2018. As there was an extremely large response to the single invitation email from the Primary Care Diabetes Lead sent in March 2018, to avoid discouraging willing practices we decided to extend the trial to include 100 practices (50 per arm). Follow-up is ongoing and linkage of practice data with referral data was completed by October 2018. It is expected that the trial will report in early 2019.

## Discussion

### Principal Considerations

While the concept of providing training in behavior change techniques and of promoting referrals to services such as weight management to staff working in primary care is not new, to date there have been no interventions that have been evaluated to assess if they are effective at improving rates of referrals and clinical outcomes for patients [17]. While the primary outcomes will be change in referral rates to weight management, secondary outcomes will include weight change and diabetes medications outcomes for referred patients, obtained via health record linkage and de-anonymized. This trial comes at a time when there is strong interest both in weight management for people with type 2 diabetes and in reducing weight stigma in health care interactions and more widely. New interventions for weight management and type 2 diabetes show very promising results [9,18,19]; however, they are Phase 2 and 3 trials with recruited volunteers. The challenge occurs when moving these interventions to real-world settings. To access the benefits of such new interventions, the patients’ usual care providers, normally primary care, will have to raise the issue and discuss weight, weight management, and know how and where to refer patients to. Unless this becomes universal, there will be inequity of access to these promising new treatments.

The trial is an evaluation of an intervention that has been developed and delivered by the health care teams usually responsible for delivering practitioner education. All email communications inviting practices to participate were sent by the usual primary care communication channels in the usual weekly newsletters. There was no separate consent process and no research visits or assessments. The entire process has been true to how it would be delivered outside of the intervention. By including 100 of 260 practices in the area, we believe it will be representative of primary care, rather than just an interested few practices.

### Limitations

One current limitation is the lack of a detailed process evaluation. We have some useful data available such as details of who has accessed the website and completed each of the modules, records of any requests for additional patient pamphlets or other materials, and full details of referral, uptake, and completion of weight management alongside electronic diabetes care records. If the intervention is not shown to be effective, it will be important to better understand what contributed to that lack of success, probably requiring interviews with practitioners and patients and even observation or recording of consultations.

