**Methods:**

We used the Behavior Change Wheel to develop an intervention for staff in primary care consisting of a 1-hour Internet-based eLearning package covering the links between obesity, type 2 diabetes, and the benefits of weight management, the treatment of diabetes in patients with obesity, specific training in raising the issue of weight, local services and referral pathways, overview of weight management components/ evidence base, and the role of the referrer. The package also includes a patient pamphlet, a discussion tool, a practice implementation checklist, and an optional 2.5-hour face-to-face training session. We have randomly assigned 100 practices in a 1:1 ratio to either have immediate access to all the resources or have access delayed for 4 months. An intention-to-treat statistical analysis will be performed.

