### Sample Size

A feasibility study was completed during which five practices (from a range of current referral rates to weight management services and deprivation areas in NHS Greater Glasgow and Clyde) were provided with access to the STBD e-learning program in June 2016. A GP and practice nurse from each attended a 2.5-hour face-to-face training session, and the practices were provided with the implementation toolkit. The referral rate to uptake was assessed for the 3 months prior to the STBD training (March-May 2016), 3 months post- STBD training (October-December 2016), and the same 3 months in 2015 (October-December 2015). We saw an increase in referrals of 50% compared to same period the year before (n=8 and 15 referrals respectively) and 88% compared to previous 3 months (n=10 and 15 referrals respectively) after the STBD intervention. Two practices did not make any referrals in the immediate time period analyzed prior to the intervention. As a result of this, together with the small number of feasibility practices, it was difficult to make a formal power calculation. The effect compared to same period 12 months before was 1.5 (SD 1.21); effect compared to 3 months previous was 1.88 (SD 0.38). A sample size of 80 per group would give 80% power to detect a difference of 0.5 in the change in referral rate based on a hypothetical SD of 1.12.

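### With 50 practices per arm, power for the planned difference is about 60%, yet the Limitations section treats an undemonstrated effect as a failure and does not list low power

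*Protocol article*

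**What the plan says.** The Sample Size section of the protocol article states: "A sample size of 80 per group would give 80% power to detect a difference of 0.5 in the change in referral rate", and adds that this is "based on a hypothetical SD of 1.12". It gives neither the significance level nor whether the test is one- or two-sided.

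The number randomised is smaller. The Methods paragraph of the abstract says "We have randomly assigned 100 practices in a 1:1 ratio", and the Results section reports a decision to "extend the trial to include 100 practices (50 per arm"). No power is given for 50 per arm.

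The Statistics section compares the arms by two-sample t tests or nonparametric equivalents.

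The Limitations section then says: "If the intervention is not shown to be effective, it will be important to better understand what contributed to that lack of success". It suggests that interviews, and possibly observing or recording consultations, would be needed to find out. The one limitation it names is that there is no detailed process evaluation.

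**The concern.** Not demonstrating an effect and demonstrating the absence of a worthwhile effect are different results. They come apart most when a trial is smaller than its own calculation requires, as this one is: 100 practices against the 160 implied by 80 per group. The Results section presents the 100 as an enlargement, so a reader could easily miss that the trial is below its stated requirement.

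The Limitations section looks ahead to a null result and assumes that its cause lies in the intervention or its delivery. Chance and limited power are not offered as explanations. The risk is that a training programme with an effect of the size hoped for is reported as unsuccessful, and that later work sets out to explain a failure that the data have not shown.

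**Working it through.** **Inputs.** Difference 0.5, SD 1.12, power 80% and 80 per group come from Sample Size; 50 per arm comes from Results. Two-sided 5% is an assumption, tested in step 1.

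**1. Reproduce the plan's figure.** By the normal approximation,
n per group = 2 × (1.960 + 0.842)² × 1.12² / 0.5² = 2 × 7.85 × 1.2544 / 0.25 ≈ 78.8, so 79.
The noncentral t solution is 79.7, so 80. The stated figure reproduces. A one-sided 5% test would need only 63 per group, so two-sided 5% is the natural reading.

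**2. Power at 50 per arm.**
SE = 1.12 × √(2/50) = 0.224.
0.5 / 0.224 = 2.232, and Φ(2.232 − 1.960) = 0.607. The noncentral t gives 0.599.
A true difference of 0.5 is therefore missed in about 40% of trials. The difference detectable with 80% power rises from 0.50 to about 0.63.

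**3. Sensitivity to the SD (50 per arm, difference 0.5, two-sided 5%).**

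| SD | Source | Power (t / normal) | Missed |
|---|---|---|---|
| 1.21 | feasibility, against same period a year earlier | 53% / 54% | 46–47% |
| 1.12 | planning value | 60% / 61% | 39–40% |
| 1.0 | illustrative | 70% / 71% | about 30% |
| 0.38 | feasibility, against previous 3 months | nearly 100% | nearly 0 |

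A one-sided 5% test at SD 1.12 would give about 72%, but that is not the basis of the stated calculation.

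**4. What a missed effect looks like.**
95% half-width = t(0.975, 98 df) × 0.224 = 0.4445.
Positive estimates up to 0.44 are non-significant, but any estimate above 0.5 − 0.4445 = 0.056 leaves the upper limit above 0.5.
If the true difference is 0.5, the upper limit falls below 0.5 in 2.5% of trials, and virtually all of those are non-significant. Among the roughly 40% non-significant trials, the share whose interval still contains 0.5 is 1 − 0.025/0.40 ≈ 94%. Simulation with 200,000 normal draws agrees (93.7% to 94.1%).

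**5. The same check with no true effect.**
The upper limit is below 0.5 in 59.9% of trials. Leaving out the 2.5% that are significantly negative, (0.599 − 0.025)/0.95 ≈ 60% of non-significant trials exclude 0.5. An interval-based reading can therefore still deliver a negative conclusion when one is warranted.

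**The case against.** The strongest reply is that the Limitations sentence is not an interpretation rule. It sits in a discussion of process evaluation, mentions neither significance nor reporting, and speaks only tentatively of what later work might need. That stands. A reader might infer that the protocol commits the trial to declaring failure whenever the test is non-significant, or rules out confidence intervals. The document says neither, and reporting detail of that kind is commonly left to an analysis plan that is not shown here.

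A reader might also infer that a non-significant result in this trial will usually be unable to exclude 0.5. That holds if the true difference is near 0.5. With no true effect, about 60% of non-significant results would exclude it.

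Two further stronger steps should be resisted. One is to treat any upper limit below 0.5 as failure. At SD 0.38 the half-width is 1.984 × 0.38 × √(2/50) ≈ 0.15, so an estimate between about 0.15 and 0.35 would be significantly positive and still have an upper limit below 0.5. The other is to withhold follow-up process work after an inconclusive result, when such work is useful then too. The protocol also uses 0.5 as a detectable difference and never calls it the smallest worthwhile effect.

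The figures are indicative. The SD is hypothetical, the protocol says a formal power calculation was difficult, the outcome is a before/after ratio, and two of the five feasibility practices made no referrals in the immediate pre-intervention period. Normal-theory power may therefore be some way off.

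Finally, the root cause is the gap between 80 and 50 per arm. That is true. But recruitment has closed, so the number of practices is settled, while the reading of a null result can still be put right.

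**Conclusion.** The point holds in a limited form. On the protocol's own inputs, 50 per arm gives about 60% power for the planned difference, against the 80% calculated for 80 per arm. A true difference of 0.5 would go undetected about 4 times in 10, and about 94% of those results would still be compatible with 0.5. The Limitations section nevertheless equates an undemonstrated effect with failure and does not name limited power.

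This rests on a two-sided 5% test (inferred because it reproduces 80 per group), SD 1.12 and approximate normality. Across SDs of 1.0 to 1.21 the chance of a miss runs from about 30% to 47%. It would vanish only if the SD were near the smaller feasibility value, on which the protocol does not plan. The weakness is in the wording and in an unacknowledged limitation; no formal decision rule is at fault.

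**What to change.** In the Limitations section:

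- State that 50 practices per arm give roughly 60% power for a difference of 0.5 under the planning SD and a two-sided 5% test, with the range for other SDs.
- Say that the arm difference will be reported with its 95% confidence interval.
- Describe a non-significant result whose interval contains 0.5 as inconclusive.
- Say that an effect of the planned size was not supported only when the result is non-significant and the upper limit is below 0.5.
- Leave follow-up process work open in both cases.

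This takes a few sentences, with no new data and no change to the test. The cost is that some null results will have to be reported as inconclusive.

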### Conclusion

We hope that if this evaluation shows that the Small Talk Big Difference intervention is effective, it will be shared with other health bodies across the United Kingdom and beyond for wide dissemination. It is locally editable and easy to update, meaning that it could be modified to fit other health systems if required.

## Abbreviations

APEASE: affordability, practicability, effectiveness/cost-effectiveness, acceptability, side-effects/safety, equity
BMI: body mass index
COM-B: Capability, Opportunity, Motivation, and Behavior
GP: general practitioner
NHS: National Health Service
STBD: Small Talk Big Difference
